### Design

This study is a randomized, 2 × 2 factorial, waiting list controlled, assessor single blinded and single-center pilot trial.

The study will be sequentially conducted as follows: enrollment after screening via inclusion and exclusion criteria, randomization, a treatment period of 4 weeks, and assessment (Figure 1).

**Figure 1 F1:**
[figure not shown]
**Flow chart of the study**.

### Participants and Eligibility

#### Inclusion criteria

According to the Korean acne grading system [30], patients are divided into 6 grades. Only grade 2 to 4 patients (with papules ≥ 10 or nodules ≤ 20, ± mild ongoing scars), who have had acne for more than 3 months (chronic stage) between the ages of 13 to 35 years, are eligible to participate in this trial.

#### Exclusion criteria

The author will exclude patients outside the normal range on blood tests, including aspartate transaminase (AST), alanine transaminase (ALT), blood urea nitrogen (Bun), creatinine, hemoglobin, and platelet (normal range: 13 ≤ hemoglobin ≤ 17 g/dl, 150000 ≤ platelet ≤ 350000/mm3, aspartate transaminase (AST) < 40 IU/L, alanine transaminase (ALT) < 40 IU/L, 8 ≤blood urea nitrogen (BUN) 23 mg/dl and 0.6 ≤ creatinine ≤ 1.2 mg/dl). Participants are ineligible if they have experienced western medical treatment or traditional medical treatment for acne within 4 weeks prior to recruitment or have keloid acne, corticosteroid acne, infectious skin disease, or internal disease requiring first aid. Participants will also be excluded if they are not willing to not comply with this study protocol. Within 4 weeks after enrollment in this trial, no concomitant acne therapy will be permitted and patients will be instructed to use non-comedogenic makeup or sunscreen.

### Recruitment

Participants will be recruited via internet advertisement posted on the website of the Kyung Hee Medical Center and via ad-posters.

### Randomization and blinding

After enrollment, participants will be randomly assigned to the waiting list (WL), acupuncture only (AO), KRTE only (KO), and KRTE combined with acupuncture treatment (KA) groups. The allocation ratio will be 1:1:1:1 in blocks of 4. Randomization will be performed at a site remote from trial location. Random numbers will be generated by a computerized random-number generator through the block-randomization method of a software program (Excel, Microsoft Office 2007) for sequence generation and we will make two separate database: a "patients" database that lists basic information such as patient name, contact details and so on, and a "randomization" database that holds data on which patients have been registered on trial along with their allocations. The "patients" database will be accessible to any researcher whereas the "randomization" database will be password protected so that it will be accessible only by the principal investigator and a nominated statistician [31]. The assessor, who will not be the acupuncture practitioner and KRTE supplier, and who is blinded to the allocation results until the end of study, will perform the outcome assessment.

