**Methods/Design:**

A randomized, assessor single blinded, 2 × 2 factorial pilot trial will be conducted. Forty four participants with acne vulgaris will be randomized into one of four groups: waiting list group (WL), KRTE only group (KO), acupuncture only group (AO), and KRTE and acupuncture combined treatment group (KA). After randomization, a total of 8 sessions of acupuncture treatment will be performed twice a week in the AO- and KA groups, respectively. Patients in the KO- and KA groups will be prescribed KRTE 3 times a day at a dose of 7.4 g after meals for 4 weeks. The following outcome measurements will be used in examination of subjects: the mean percentage change and the count change of inflammatory and non-inflammatory acne lesions, the Skindex 29, visual analogue scale (VAS) and investigator global assessment (IGA) from baseline to the end of the trial.

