#### Waiting list group

Participants who will be assigned to the WL group will not receive any acupuncture or KRTE treatment throughout the 4-week post-randomization period. After the end of the study, if participants elect to undergo acupuncture treatment, it will be provided twice weekly for 4 weeks.

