### Sample size

This study is a pilot study for evaluation the interaction and efficacy of KRTE and acupuncture in male patients with acne vulgaris and the feasibility of a large clinical trial. Because this trial was designed to be of short duration, lasting four weeks, with the intention of decreasing the drop-out rate, the desired sample size for this pilot study is 44 patients, with 11 for each group, assuming a drop-out rate of 10%.

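### One disclosed block size of 4 for four visibly different arms leaves allocation concealment open to prediction

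*Protocol article*

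**What the plan says.** The Randomization and blinding section of the protocol article fixes the scheme: "The allocation ratio will be 1:1:1:1 in blocks of 4". No second block size is given, and nothing says that the size is withheld from recruiting staff. The abstract gives the total: "Forty four participants with acne vulgaris will be randomized into one of four groups". The Sample size section gives 11 per group.

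The Design section describes the study as a "waiting list controlled, assessor single blinded and single-center pilot trial". There is no sham or placebo. The AO and KA groups receive needles, the KO and KA groups receive the herbal extract, and waiting-list patients "will not receive any acupuncture or KRTE treatment throughout the 4-week post-randomization period".

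The same randomization section sets out safeguards:
- Assignment follows enrolment.
- "Randomization will be performed at a site remote from trial location".
- A separate, password-protected database holds registered patients with their allocations, and "it will be accessible only by the principal investigator and a nominated statistician".
- The assessor neither gives acupuncture nor supplies the extract, and stays blinded to the end of the study.

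**The concern.** When the block size equals the number of arms, every block is one ordering of the four arms. Once three patients in a block are allocated, the fourth arm is known. At one centre with no stratification stated and open treatments, past allocations can be learned by watching who receives needles, extract, both or nothing. The block size is printed in the protocol, and the Acupuncture section says the practitioners' training course covers the protocol.

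Someone who can foresee the next arm can bring forward, delay or turn away a candidate. The Exclusion criteria leave some room for this, since one criterion is a judgement about willingness to comply. The distinction most likely to tempt is waiting list against active treatment, because waiting-list patients go four weeks without study treatment. With 11 patients per arm, a few steered patients could move an arm mean. The planned ANCOVA adjusts for baseline and other measured covariates, but it cannot remove selection on features that nobody records.

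**Working it through.** **Inputs.** Four arms at 1:1:1:1 in blocks of 4 (Randomization and blinding); 44 patients, 11 per arm (abstract, Sample size). *Assumption for all figures below:* the guesser knows the block size and every earlier allocation in the current block, and always names an arm with the most places left.

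**The plan's own figure.** 4 arms × 11 = 44 patients, and 44 / 4 = 11 complete blocks. The total and the block size agree. The total of 44 is not in dispute here.

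**Certain allocations.** Only the fourth place in a block is fully determined: 1 per block × 11 blocks = 11 of 44 = 25%.

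**Correct guesses.** The chance of a correct guess at places 1 to 4 is 1/4, 1/3, 1/2 and 1.
- Sum per block: 0.250 + 0.333 + 0.500 + 1.000 = 2.083
- Share: 2.083 / 4 = 52.1%
- Over 11 blocks: 2.083 × 11 = 22.9 of 44
- Simple randomization: 1/4, or 11 of 44

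**Waiting list or active.** The status is certain if the waiting-list place has already been used, or if only that place remains.

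| Place in block | Certain not waiting list | Certain waiting list | Status certain |
|---|---|---|---|
| 1 | 0 | 0 | 0 |
| 2 | 1/4 | 0 | 1/4 |
| 3 | 1/2 | 0 | 1/2 |
| 4 | 3/4 | 1/4 | 1 |
| Sum per block | 1.50 | 0.25 | 1.75 |
| × 11 blocks | 16.5 | 2.75 | 19.25 |

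So the status is certain for 1.75 / 4 = 43.75% of allocations, about 19 of 44. Most of this is knowledge that the next patient will be treated. Certainty that the next patient goes to the waiting list arises in 2.75 of 44, about 6%.

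**Alternatives under the same assumption.** For a block of B patients with m = B/4 per arm, the final run with only one arm left has expected length B / (B − m + 1). The share of certain allocations is therefore 1 / (B − m + 1). Correct guesses come from exact enumeration of the permuted block.

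| Scheme | Certain | Guessed correctly |
|---|---|---|
| Block of 4 | 1/4 = 25% | 2.083 / 4 = 52.1% |
| Block of 8, size known | 1/7 = 14.3% | 3.760 / 8 = 47.0% |
| One list of 44 | 1/34 = 2.9% | 15.92 / 44 = 36.2% |
| Simple randomization | 0% | 25% |

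A larger block of known size helps only moderately. No figure was computed for an undisclosed mix of sizes. Its benefit comes from the guesser no longer knowing where a block ends.

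**The case against.** A reader might infer that concealment is broken, that every fourth allocation is certain in advance, and that the principal investigator can look up the next arm. The document supports none of these as stated.

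- *Safeguards exist.* Assignment after enrolment, remote randomization and a password-protected database are all stated. They keep the list itself from recruiting staff. This stands, and it rules out calling concealment broken. It does not answer prediction, which uses allocations already revealed and acts on the next candidate before enrolment.
- *The database is described as a record of the past.* It holds registered patients with their allocations; a future sequence is not mentioned. Nor does the document say that the principal investigator screens or enrols. Knowing past assignments in an open trial is not in itself a breach. This stands: the access is not a separate failure and matters only by supplying what a block-based deduction needs.
- *Certainty is conditional.* No passage says that one recruiting person sees all four arms in order. Pooling that knowledge at one centre is plausible, but it is an assumption.
- *Simple randomization is a generous benchmark.* The remedy does not reach 25%; one list of 44 still gives 36.2%. This also stands, so the gain should be judged against 36.2%.
- *It is a pilot with a blinded assessor and lesion counts from photographs.* These protect measurement. They do not protect the choice of who enters which arm.

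**Conclusion.** The point holds in a limited form. A single disclosed block size of 4, with four distinguishable arms at one centre, lets an informed person deduce 11 of 44 allocations (25%) and guess 52.1% correctly. Waiting-list or active status would be certain for about 19 of 44: about 16.5 certain to be treated and about 2.75 certain to be waiting list. These figures are exact for someone who knows the block size and the earlier allocations in the block; for anyone else, predictability is lower.

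Concealment is therefore left open to prediction, not shown to be broken. The principal investigator's database access adds to this only if that person takes part in screening or enrolment, on which the document is silent. Whether anyone would act on a prediction, and how large the bias would be, cannot be derived from the documents. The change is still worth making: it is cheap, and the method may carry over to the large trial whose feasibility this pilot is meant to assess.

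**What to change.** Before the first patient is enrolled, replace the scheme in one of two ways:

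1. Use randomly varying block sizes in multiples of 4, for example 4 and 8. State in the protocol only that sizes vary, and keep the sizes and their order from site staff.
2. Use one permuted list of 44 with 11 per arm. This cuts certain allocations from 25% to 2.9% and correct guesses from 52.1% to 36.2%, and still ends at 11 per arm.

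Keep remote randomization and assignment after enrolment. Until enrolment is complete, limit the randomization database to the statistician or off-site allocator, or to people who do not screen or enrol. State who enrols, and that the future sequence is withheld from them.

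The cost is a new list and a small change in access rights. The downside is some arm imbalance if recruitment stops early. It should be slight with blocks of 4 and 8, and may be larger with a single list.

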### Intervention

#### KRTE

KRTE is approved by the Korea Food and Drug Administration as a prescription in clinical practice for patients with sinusitis, otitis media, and acne. The components of KRTE are presented in Table 1. The authors purchased KRTE from the Han Kook Sin Yak Pharm. Co., which is equipped with a Korean good manufacturing practice (KGMP) facility. Participants in the KO and KA groups will be prescribed KRTE three times a day at a dose of 7.4 g after meals for 4 weeks.

**Table 1 T1:** Components of KRTE (7.4 g/dose)

Scientific Name	Amount (g)
*Schizoneptae Herba*	0.27
*Forsythiae Fructus*	0.34
*Ledebouriellae Radix*	0.65
*Angelicae gigantis Radix*	0.70
*Cnidii Rhizoma*	0.65
*Paeoniae Radix*	0.32
*Bupleuri Radix*	0.59
*Aurantii Fructus*	0.86
*Scutellariae Radix*	0.67
*Gardeniae Fructus*	0.89
*Angelicae dahuricae Radix*	0.35
*Platycodi Radix*	0.51
*Glycyrrhizae Radix*	0.67
**Total**	**7.40**

#### Acupuncture

Certified acupuncture practitioners who have a minimum of 3 years of clinical experience obtained after a 6-year oriental medical college course will perform the acupuncture treatment. They will take a one-day training course for this trial. This course will include the study protocol, methods for acupuncture treatment, and basic information on clinical research. Eight sessions of acupuncture treatment will be performed twice per week for four weeks in patients who will be assigned to the AO and KA groups. Patients will receive acupuncture treatment at 11 classical acupuncture points and/or *ah shi *points that were randomly selected at papules and nodules on the face by the acupuncture practitioner. The following 11 acupuncture points will receive bilateral treatment: ST2 (*Sibai*), ST6 (*Jiache*), ST36 (*Zusanli*), LI20 (*Yingxiang*), LI11 (*Quchi*), PC6 (*Neiguan*), HT8 (*Shaofu*), SP3 (*Taibai*), SP6 (*Sanyinjiao*), SP10 (*Xuehai*), and LR3 (*Taichong*). These points will be treated with 0.25 × 30 mm disposable acupuncture needles (Dongbang Co., Korea). Selection of these acupuncture points was based on a literature review and previous studies of acupuncture treatment of acne vulgaris [20,21] and from the attending doctor's clinical experience and they will be located according to WHO standard Acupuncture Point Locations in the Western Pacific Region [32]. Patients will remain in a supine position for 15 minutes during acupuncture treatment. Papules and nodules will not be artificially extruded.

#### Waiting list group

Participants who will be assigned to the WL group will not receive any acupuncture or KRTE treatment throughout the 4-week post-randomization period. After the end of the study, if participants elect to undergo acupuncture treatment, it will be provided twice weekly for 4 weeks.

### Outcome measures

#### Primary outcome

Primary outcome will be presented by the mean percentage change of inflammatory lesion counts from baseline to the end of the trial [29,33].

#### Secondary outcomes

Secondary outcomes will be shown by the mean percentage change of non-inflammatory lesion counts from baseline to the end of the trial, count of inflammatory and non-inflammatory lesions, the quality-of-life scale (Skindex-29), Visual Analogue Scale (VAS) [score 0 (no symptoms) to 100 (severe symptoms)], and the Investigator Global Assessment [IGA; after evaluation from score 1 (very good) to 5 (very poor) every session, we divided into 'improvement' or 'non-improvement' between baseline and the end of the study]. Skindex 29 will be checked at weeks 0 (baseline) and 4 (end of the trial). VAS and IGA will be checked every session from baseline (just before randomization) and through the 4 weeks after randomization. A Lumix DMC-LX2 digital camera (Panasonic, Osaka, Japan) was used to photograph each patient's face, so that inflammatory and non-inflammatory lesions could be counted at weeks 0 (baseline) and 4 (end of the trial).

### Statistical methods

#### Statistical analysis plan

Statistical analysis will be conducted on an intension-to-treat basis with a 95% confidence interval using SPSS version 12.0 for Windows. Missing values of drop-out participants will be imputed by the last observation carried forward (LOCF) method. Data will be displayed as the mean ± standard deviation (SD) for continuous data or n (%) for categorical data.

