#### Baseline data and Outcome data

A two-way analysis of covariance (ANCOVA) test will be used to examine the percentage change of inflammatory and non-inflammatory lesions from baseline to the end of the trial when controlling for baseline and other covariates. A repeated measured ANCOVA test will be performed for evaluation of any significant difference in count of inflammatory and non-inflammatory lesions, Skindex-29 score, and VAS score between baseline and the end of the trial. If there is an interaction between KRTE and acupuncture, only the interaction will be shown. If not, the main effect of KRTE and acupuncture will be reanalyzed and presented. According to 'improvement' or 'no-improvement' of IGA score between baseline and the end of the trial, the difference among the groups will be evaluated using a Chi-square test or Fisher's exact test.

Proportion of drop-outs and compliance with KRTE and questionnaire completion will be calculated and described as n (%). The percentage of subjects in each group will be compared using a Chi-square test or Fisher's exact test.

All adverse events reported during the study will be included in the case report forms; the incidence of adverse events will be calculated. The percentage of subjects with adverse events in each group will be calculated and compared using a Chi-square test or Fisher's exact test.

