#### Compliance

KRTE remaining after each session will be quantified in order to enhance medication compliance. Participants whose compliance with KTRE is ≤ 80% of the total dose or who receive fewer than six acupuncture sessions will be considered to have dropped-out.

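### With lesion counts only at weeks 0 and 4, LOCF becomes baseline carried forward: a missing week-4 count scores exactly 0% change on the primary outcome

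*Protocol article*

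**What the plan says.** All places are in the Protocol article.

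- Primary outcome: "Primary outcome will be presented by the mean percentage change of inflammatory lesion counts from baseline to the end of the trial".
- Secondary outcomes: faces are photographed so that "inflammatory and non-inflammatory lesions could be counted at weeks 0 (baseline) and 4 (end of the trial"). Skindex-29 has the same two time points. VAS and IGA differ: "VAS and IGA will be checked every session from baseline (just before randomization) and through the 4 weeks after randomization".
- Statistical analysis plan: "Statistical analysis will be conducted on an intension-to-treat basis with a 95% confidence interval using SPSS version 12.0 for Windows". The next sentence gives the only missing-data rule, with no exception for any outcome: "Missing values of drop-out participants will be imputed by the last observation carried forward (LOCF) method".
- Baseline data and Outcome data: "A two-way analysis of covariance (ANCOVA) test will be used to examine the percentage change of inflammatory and non-inflammatory lesions", adjusting for baseline and other covariates. The interaction result decides whether main effects are presented.
- Compliance: a participant who takes 80% or less of the KRTE dose counts as a drop-out, and so do those "who receive fewer than six acupuncture sessions will be considered to have dropped-out".
- Sample size: "the desired sample size for this pilot study is 44 patients, with 11 for each group, assuming a drop-out rate of 10" per cent.

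**The concern.** LOCF needs a measurement between baseline and the final visit to do what its name suggests. The lesion counts have none. For a participant with no week-4 count, the last observation is the baseline count, and the imputed percentage change is zero whatever the arm and whatever the course of the acne up to withdrawal. The ANCOVA then treats that zero as a measured outcome.

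Two things are at stake. If losses are equal across arms, every effect is pulled towards zero. If they are unequal, the contrasts move by an amount that reflects who left and not what the treatments did. Unequal loss is plausible here. The compliance rule can sensibly apply only to treated arms, since the waiting list receives neither KRTE nor acupuncture, and combined-arm participants can fail on either criterion. The interaction is the first null hypothesis in the Objective section and determines how the rest of the results are reported, so a shift there has consequences beyond one estimate.

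**Working it through.** **The plan's own figures.** At 10% drop-out, 11 × 0.9 = 9.9 participants remain per arm and 44 × 0.9 = 39.6 in total, so about one is lost per arm and four overall. The article gives no effect size, SD or power, so 44 cannot be rebuilt from a power formula. Nothing below depends on that.

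**Step 1: the imputed value.** Let Y0 and Y4 be the counts at weeks 0 and 4. If Y4 is missing, LOCF sets Y4 = Y0, and the change is 100 × (Y0 − Y0)/Y0 = 0%. This holds for any baseline count; 10, 20 and 40 lesions all give 0%.

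**Step 2: equal losses.** With k imputed zeros among 11, arm mean = (1 − k/11) × mean of the others. The factor is 10/11 = 0.909 for k = 1, 9/11 = 0.818 for k = 2 and 8/11 = 0.727 for k = 3. With k = 1 in every arm, all contrasts shrink by 0.909; an assumed main effect of −20 points becomes −20 × 10/11 = −18.2.

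**Step 3: unequal losses.** Assume, since the article gives no figure, that every arm truly improves by the same amount, 20% to 40%, so all true contrasts are zero. If k are missing in one arm and none in its comparator, the spurious difference is k/11 × the true improvement.

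| Missing | True improvement 20% | True improvement 40% |
|---|---|---|
| 2 vs 0 | 2/11 × 20 = 3.6 points | 2/11 × 40 = 7.3 points |
| 3 vs 0 | 3/11 × 20 = 5.5 points | 3/11 × 40 = 10.9 points |

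The difference goes against treatment if the losses are in the treated arm and favours it if they are on the waiting list. These are arm-against-arm figures. When only one arm has losses, the interaction KA − KO − AO + WL moves by the full amount, and a factorial main effect, which averages two such differences, by half.

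**Step 4: a false interaction.** Assume additive true means WL/KO/AO/KA = −10/−30/−30/−50, so the KRTE main effect is −20 and the interaction is 0. Let 0/1/1/2 be missing.

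- Arm means become −10, −30 × 10/11 = −27.27, −27.27 and −50 × 9/11 = −40.91.
- KRTE main effect = [(−27.27 + 10) + (−40.91 + 27.27)]/2 = −15.5.
- Interaction = −40.91 + 27.27 + 27.27 − 10 = +3.6, where the truth is 0.

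**Step 5: precision.** With four cells and one covariate, residual degrees of freedom are 44 − 5 = 39 with the imputed rows and 40 − 5 = 35 without them.

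Steps 2 to 4 use unadjusted means and assume that those missing would have changed like the rest of their arm. Baseline adjustment would alter the figures somewhat in any one sample but does not remove the zeros.

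**The case against.** The strongest reply has four parts.

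**Not every drop-out is affected.** A reader might infer that each participant classed as a drop-out receives 0%. The documents do not support that. LOCF fills missing values only, and someone classed as a drop-out for low compliance may still have a week-4 photograph. The article does not say whether such a count is kept or discarded. The point holds for those whose count is missing, or is discarded under that rule. Likewise, if the full protocol arranges a lesion count at early withdrawal, which the article does not mention, that value would be carried forward.

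**The standard error.** A reader might infer that the imputed rows make standard errors too small by a known factor. They do not. The zeros raise the number of rows but also change the spread, and no SD is given. With one zero in 11, a mean change of −20 and an SD of 40, the SD becomes 38.6 and the arm's SE falls from 40/√10 = 12.6 to 38.6/√11 = 11.6. With a mean of −40 and an SD of 20, the SD becomes 22.3 and the SE rises from 6.3 to 6.7. The direction is not established.

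**The effect is modest and conservative in a pilot.** At a balanced 10% this is fair: about four participants and a 9% shrinkage. It does not cover imbalance, which can favour treatment when the losses are on the waiting list. The offer of acupuncture after the study gives waiting-list participants a reason to stay, and the single 10% rate does not predict imbalance, so imbalance is plausible and not certain. Pilot status does not settle the matter, because the Objective section sets formal null hypotheses on this outcome.

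**The unseen SAP.** It may hold sensitivity analyses, and their absence here is no criticism. The article does state a specific method, however, and that method does not fit its own measurement schedule.

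**Conclusion.** As written, the missing-data rule is baseline carried forward for the primary outcome. The same is true of percentage change and counts of non-inflammatory lesions, of inflammatory lesion counts and of Skindex-29. VAS and IGA, recorded every session, are not affected in this way.

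That part follows from the text alone. The size rests on assumptions. Near the plan's 10% and with balanced losses, the shrinkage factor is 0.909. The spurious 3.6 to 7.3 points (2 vs 0 missing) and 5.5 to 10.9 points (3 vs 0) need true improvements of 20% to 40%, which the article does not give. The false interaction of +3.6 belongs to one assumed set of means and losses. The documents support neither a fixed direction of bias nor a claim that the waiting list would improve spontaneously.

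This should be fixed before analysis. With 11 per arm, each imputed zero is 1/11 = 9% of an arm's data on the primary outcome.

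**What to change.** Replace LOCF as the primary method for every outcome measured only at weeks 0 and 4.

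- Keep percentage change as the outcome, so that its scale is unaltered. Fit the planned two-way ANCOVA with the baseline covariate to all participants with an observed week-4 count, analysed in the group to which they were randomised.
- State that a week-4 count from a participant classed as a drop-out for low compliance is used as observed, neither discarded nor imputed.
- Retain baseline carried forward as a labelled sensitivity analysis. Multiple imputation is an option if the model is kept small (arm, baseline count and few auxiliary variables). With about 10 completers per arm, a separate model per arm with many session scores would be unstable. Any session VAS or IGA score used should first be confirmed to exist in the waiting-list arm, which has no treatment sessions.

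The cost is a change of wording and a little extra analysis, with no new visits or data. The primary model's N falls to the number observed, about 40 of 44 at 10% drop-out. The analysis is valid if missingness depends only on arm and baseline, which the data cannot confirm; this is the reason to keep the sensitivity analysis.
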